### Protocol and Randomization

ACTNOW will have two waves involving different cohorts, the first running from August 2019 to June 2021, and the second from August 2020 to June 2022 (Figure 3). The professional development provided in Wave 2 will be adjusted based on experiences and findings from Wave 1. Data collection will have three main stages; pre-testing performed before randomization, 7-month follow-up performed at the end of the professional development, and 18-month follow-up performed 1 year after staff have completed the professional development. In addition, process evaluation measures will be taken throughout the study.

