**FIGURE 3 F3:**
[figure not shown]
Flow chart of the study.

We will cluster randomize at the preschool level, since we regard delivery of the intervention on the preschool level the only practical approach. A third party ([name], Norwegian School of Sport Sciences) will randomize ≈ 60 preschools to the intervention group (≈ 30 preschools) or the standard of care control group (≈ 30 preschools). Randomization will be done separately in the two study waves after completing recruitment and before initiating baseline data collection using a random number generator (Stata/SE 15.1, StataCorp LLC, College Station, TX, United States). We will use block randomization (randomly chosen block sizes of 4 and 6) and a 1:1 ratio for the two intervention arms. Blinding of participants and preschools is not possible due to the nature of the experiment. To limit potential biases, the fewest possible assessors involved in project management, data collection, and statistical analysis will have knowledge about the group assignment and the study hypotheses.

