#### Data Management

High-quality data collection, data management, and data analysis is of crucial importance to ensure valid study results and secure privacy protection of participants. Prior to the data collection, all assessors will perform thorough training in how to instruct and score children on the different measures to ensure high interrater reliability and minimal measurement error.

Non-digital data on main child-level outcomes (anthropometry, physical fitness, motor competence, and self-regulation) will be double-checked for 100% of cases and triple-checked for a random sample of 10% of cases. Other sources of non-digital data will be double-checked using a random sample of 25% of preschools. After the thorough quality control of data, the database will be locked prior to opening the group allocation (1- and 2-years follow-up) and prior to performing any statistical analysis.

Data handling and storage are confidential and will be managed according to the Western Norway University of Applied Sciences internal control system in accordance with Norwegian privacy protection regulations/the General Data Protection Regulation (EU 2016/679).

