### Analysis Plan

#### The Child Level

##### Primary aim

The main analyses of child-level effects will employ an intention-to-treat principle, thus including all subjects and preschools originally allocated to the respective groups, to test the study’s effectiveness (Polit and Gillespie, 2010). However, as shown for the school setting (Donnelly et al., 2009), there are strong arguments for including per-protocol analyses for the examination of efficacy. Therefore, we will perform secondary analyses limited to preschools that exhibit acceptable intervention adherence. Missing data will be sought, minimized, detailed, and handled in line with suggested guidelines (Little et al., 2012). Attrition analyses will be performed to investigate whether missing data are related to child characteristics. Missing data will be handled by the use of linear mixed models (LMMs) and structural equation modeling (SEM) (Enders, 2011; Little, 2013).

Intervention effects will be evaluated by testing for time^∗^group interactions for all outcomes. The per-protocol analysis will be adjusted for differences between the groups, as appropriate. LMM and multilevel SEM for mediation analyses (SEM) (Little, 2013) will be used to account for clustering of observations on the preschool level in all analyses. A two-sided *p* ≤ 0.05 is considered statistically significant; however, both ESs and patterns of effects across variables will be considered of greater importance than *p*-values when drawing study conclusions. Consistent with this approach, *p*-values will not be adjusted for multiple testing. Main analyses will be performed using IBM SPSS v. 25 (IBM SPSS Statistics for Windows, Armonk, NY: IBM Corp., United States) or later versions and MPLUS v. 8 or later versions (Muthén and Muthén, Los Angeles, United States). Reporting will be done in accordance with the CONSORT statement (Campbell et al., 2012).

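### Wave stratifies the randomization and the programme is revised between waves, but the stated effect analysis and moderator list do not say how wave is handled

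*Protocol article*

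**What the plan says.** Under Protocol and Randomization the article states: "ACTNOW will have two waves involving different cohorts". The first runs from August 2019 to June 2021 and the second from August 2020 to June 2022. Under Participants, the birth years are 2014–2016 for Wave 1 and 2015–2017 for Wave 2. On allocation: "Randomization will be done separately in the two study waves" and "We will use block randomization (randomly chosen block sizes of 4 and 6) and a 1:1 ratio for the two intervention arms". On the intervention: "The professional development provided in Wave 2 will be adjusted based on experiences and findings from Wave 1".

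The effect analysis is described under Analysis Plan, Primary aim. "Intervention effects will be evaluated by testing for time" by group interactions, for every outcome. Linear mixed models and multilevel structural equation models "will be used to account for clustering of observations on the preschool level in all analyses". The only adjustment mentioned is "The per-protocol analysis will be adjusted for differences between the groups, as appropriate". Under Secondary analyses of intervention effects, the moderators fixed in advance are sex, age, socioeconomic status and the baseline level of the outcome.

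The sample size under Participants is a single calculation for about 60 preschools, with no split by wave. The word wave does not occur in the Analysis Plan.

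**The concern.** Separate randomization in each wave makes wave a stratum of the design. The two strata differ in preschools, birth cohorts and calendar period. The usual practice is to carry a stratification factor into the main model. Otherwise any difference between strata stays in the residual between-preschool variation, although the randomization has already removed it from the comparison of arms.

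The second issue is interpretation. The professional development is the main intervention, and the plan is to change it between waves. A pooled time-by-group effect is then an average over the initial and the revised programme. The introduction asks how, why and for whom the intervention works, and the Dissemination section foresees offering the programme long term if it succeeds. Readers would want to see the two versions side by side, and no such presentation is planned.

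**Working it through.** **Reproducing the plan's own figures.** Inputs from Participants: 13 children per preschool, coefficient of variation of cluster size 0.65, 30 preschools per arm, ICC 0.05–0.10, correlation of repeated measurements r = 0.6–0.7, about 400 children per arm, two-sided 5% level, 80% power.

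- Design effect = 1 + (1 + 0.65² × 29/30) × (13 − 1) × ICC = 1.845 at ICC 0.05 and 2.690 at ICC 0.10. The article gives 1.85–2.69.
- Detectable d for a change contrast = 2.80 × √(4(1 − r) × 2.69/400) = 0.291 at r = 0.6 and 0.252 at r = 0.7. The article gives 0.25–0.30.

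The sample size is therefore reproduced, on a change-score basis and without wave. The point about wave alters none of these figures.

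**Which wave difference matters.** A time-by-group test compares change. With complete data, a stable difference in level between waves cancels out of change. Only a difference in change adds error, so the term that matters is wave-by-time.

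**Size of the effect on the standard error.** Assume ICC 0.10, r = 0.65 (midpoint of the article's range), 13 children in every preschool, and 30 preschools in each wave.

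- Variance of a preschool's mean change = 2(1 − 0.65) × (0.10 + 0.90/13) = 0.1185.
- SE of the arm difference = √(0.1185 × 2/30) = 0.089.
- If change differs by w between equal waves and wave is omitted, the residual variance rises by w²/4.
- For w = 0.2: √((0.1185 + 0.010) × 2/30) = 0.093.
- For w = 0.4: √((0.1185 + 0.040) × 2/30) = 0.103.

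The true sampling spread stays near 0.089, because blocking within wave balances the arms. The reported SE is too large, and the estimate is unaffected.

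**Simulation.** Preschool-mean change scores, 60 preschools, blocks of 4 and 6 within wave, 6,000 runs per setting, true effect 0 (type I error) or 0.25 (power):

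| Wave difference in change (assumed) | Preschools per wave | Type I error, without / with wave | Power, without / with wave |
|---|---|---|---|
| 0 | 30/30 | 0.050 / 0.049 | 0.784 / 0.784 |
| 0.2 SD | 30/30 | 0.041 / 0.050 | 0.772 / 0.801 |
| 0.4 SD | 30/30 | 0.026 / 0.050 | 0.694 / 0.796 |
| 0.2 SD | 20/40 | 0.039 / 0.045 | 0.774 / 0.795 |

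In a further setting the effect itself also differed by 0.2 between waves (0.15 and 0.35, averaging 0.25), with w = 0.2. Both models then estimated 0.251, with power 0.727 without wave and 0.784 with it. No setting showed bias. The largest difference between arms in the share of Wave 2 preschools was 0.067.

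The Monte Carlo error of a power near 0.78 is √(0.78 × 0.22/6000) ≈ 0.005. Because cluster sizes were equal in the simulation, the absolute power is somewhat optimistic; the comparison within each row is what counts.

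**Precision of a by-wave comparison.** With equal waves, each wave's effect has √2 times the SE of the pooled effect, and the difference between waves has twice that SE. If the pooled effect is powered for 0.25, its SE is 0.25/2.80 = 0.089. The wave-by-group SE is then about 0.18 and the 95% CI about ±0.35 SD.

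**The case against.** The strongest objection is that silence is not a decision. The article names the tested contrast and the clustering level but does not list every fixed effect, and covariates are commonly settled in a fuller plan that is not shown. This stands: a reader might infer that the investigators have chosen to pool the waves without a wave term, and the text does not say so. What remains is that the article publishes its effect test and its moderators, and neither acknowledges a stratum and a change of programme that the same article introduces.

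Three other stronger readings are tempting and are not supported.

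- *Bias or imbalance from unfinished blocks.* The simulated imbalance was negligible and the estimates were unbiased.
- *A large loss of precision from differences in level between waves.* That calculation uses preschool means at a single time, whereas the planned contrast is change.
- *A conflict between revising Wave 2 on Wave 1 findings and the rule under Data Management that "the database will be locked prior to opening the group allocation (1- and 2-years follow-up) and prior to performing any statistical analysis".* The section on staff experiences uses the word findings for Wave 1 qualitative results, and process measures run throughout. Nothing says that comparative outcome data would inform the revision.

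It is also fair to say that variation in the programme is part of this realist, co-created design, that preschool-level variation will be explored, and that the listed moderators concern child characteristics. A by-wave estimate will also be imprecise. These points argue for a descriptive reading. They do not argue against showing the two versions.

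**Conclusion.** The point holds as a matter of efficiency and interpretation. It is not a threat to validity. As written, the analysis does not state how wave enters, although wave stratifies the randomization and marks a planned change in the intervention. If it is omitted, the test is valid but conservative. The cost is nil when change is the same in both waves, about 3 percentage points of power at an assumed 0.2 SD difference, and about 10 points at 0.4 SD. These sizes rest on assumed wave differences, since the article gives none, and on ICC 0.10, r = 0.65, equal cluster sizes and a true effect of 0.25. Separately from power, the pooled effect averages two programme versions that readers cannot tell apart from the planned reporting.

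**What to change.** State that the main models include wave and wave-by-time as fixed effects. Wave-by-time does the work for a time-by-group contrast; a wave main effect alone would do little. Report the intervention effect separately for each wave, with a wave-by-group(-by-time) estimate and 95% CI. Say in advance that this comparison is descriptive, because its SE is about twice that of the main effect.

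The cost is one or two model degrees of freedom for a given follow-up, set against about 60 preschools, and one extra table row. No new data are needed, and the simulation showed no loss of power when the waves do not differ.

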### Participants

We will invite all preschools (both public and private) in multiple regions in the county of Sogn og Fjordane, Norway, having ≥ six 3- to 4-year-old children (i.e., requiring a minimum number of children available for 2-year follow-up) to participate in the study. We will invite all 3- to 5-years-old children enrolled in these preschools (Wave 1: children born 2014–2016; Wave 2: children born 2015–2017). Children who are unable to take part in normal everyday PA as promoted by the preschools as part of the intervention will be excluded from the analyses.

Sample-size calculations are derived from standardized ESs in meta-analyses of interventions investigating preschoolers’ objectively measured PAs (Finch et al., 2016) and motor competences (Wick et al., 2017), and schoolchildren’s cognition (Alvarez-Bueno et al., 2017b) and learning (Alvarez-Bueno et al., 2017a). Preschool interventions have shown small ESs for long-term interventions delivered by preschool staff targeting PA [ES = 0.07 (three studies, > 6 months) and 0.27 (10 studies, delivered by teachers)] (Finch et al., 2016) and motor competence [ES = 0.32 (six studies, vs 6 months) and 0.41 (eight studies, delivered by teachers)] (Wick et al., 2017). Rather similar ESs are shown for cognition (0.11-0.30) (Alvarez-Bueno et al., 2017b) and learning outcomes (0.16-0.26) (Alvarez-Bueno et al., 2017a) in older children (4-18 years). Derived from a conservative sample-size calculation using standard formulas, including correction for the cluster RCT design, we aim to recruit a minimum of 60 preschools and 800 3- to 4-year-old children to the study. This sample size will allow for uncovering statistically significant standardized ESs (Cohen’s d) of 0.25-0.30 at the 18-month follow-up, given *ɑ* = 0.05, 1-β = 80%, group ratio 1:1, correlation of repeated measurements = 0.6-0.7, intra-class correlation (ICC) across clusters = 0.05-0.10, children per cluster = 13 accounting for 30% attrition among children (median number of 3- to 4-years-old in preschools in Sogn og Fjordane ≈ 18), and coefficient of variation for cluster sample size = 0.65 (Eldridge et al., 2006). Thus, we will require ≈ 400 children and 30 preschools for analysis in each group (intervention; control), given a design effect correction factor = 1.85-2.69. The ICC is estimated using a mean ICC = 0.05 for trials investigating objectively measured PA levels in preschoolers (Finch et al., 2016), results from the Sogn og Fjordane Preschool Physical Activity Study: ICC ≤ 0.10 for PA (Nilsen et al., 2019b) and ICC ≤ 0.05 for motor competence (unpublished), and ICC = 0.07-0.09 for academic performance in schoolchildren (Resaland et al., 2016). Because the sample-size calculation is performed for the 18-month follow-up of 3- to 4-years-old, we will have increased power at the 7-month follow-up, as we also include 5-years-old (minimum total *n* ≈ 1,200 children); ESs as low as 0.20 can be detected at the 7-month follow-up under the assumptions specified above.

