**Methods:**

The study will be conducted in Norway 2019–2022 and is designed as a two-arm (intervention, control) cluster randomized controlled trial (RCT) with 7- and 18-months follow-ups. We aim to recruit 60 preschools and 1,200 3- to 5-years-old children to provide sufficient power to detect effect sizes (ESs) between 0.20 and 0.30. The intervention is nested within two levels: the preschool and the child. Central to the ACTNOW intervention are opportunities for children to engage in a variety of “enriched,” meaningful, and enjoyable physically active play that supports the development of the whole child. To this end, the main intervention is a 7-month professional development/education module for preschool staff, aimed to provide them with the necessary capacity to deliver four core PA components to the children (moderate-to-vigorous PA, motor-challenging PA, cognitively engaging play, and physically active learning). We will include a range of child-level outcomes, including PA, physical fitness, adiposity, motor skills, socioemotional health, self-regulation, executive function, and learning. At the preschool level, we will describe implementation and adaptation processes using quantitative and qualitative data.

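### The same figure, about 800 children aged 3 to 4, serves as both the recruitment minimum and the number required for analysis after 30% attrition; the power cost is modest

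*Protocol article*

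**What the plan says.** All the sample-size figures stand in the Participants section of the protocol article. The recruitment aim is put this way: "we aim to recruit a minimum of 60 preschools and 800 3- to 4-year-old children to the study". The cluster size behind the calculation is "children per cluster = 13 accounting for 30% attrition among children", taken from a median of about 18 children aged 3 to 4 per preschool. After giving a detectable d of 0.25-0.30 at 18 months, the section concludes that "we will require ≈ 400 children and 30 preschools for analysis in each group", with a design effect of 1.85-2.69.

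For 7 months, 5-year-olds are added to reach a minimum total of about 1,200, and the section states that "ESs as low as 0.20 can be detected at the 7-month follow-up under the assumptions specified above". The abstract gives 60 preschools and 1,200 children as the recruitment aim, "to provide sufficient power to detect effect sizes (ESs) between 0.20 and 0.30".

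**The concern.** About 800 children cannot be both the number recruited and the number left after 30% have dropped out. If 800 is the intake, the analysed sample is 30% smaller than the one behind the stated power. If 800 is the analysed number, the recruitment target is too low. A trial could then meet its published minimum and still fall short of the number it says it requires, and readers would judge small or null effects against detectable effects computed for a larger sample.

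The 1,200 raises the same question: the abstract makes it a recruitment figure, while the Participants section uses it as the total behind the 7-month effect.

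**Working it through.** **Inputs** (Participants section unless noted): "1-β = 80%, group ratio 1:1"; two-sided 5% level (Primary aim, in the Analysis Plan); 60 preschools, 30 per arm; ICC 0.05-0.10; correlation r between repeated measurements 0.6-0.7; coefficient of variation (CV) of cluster size 0.65; 18 children per preschool before and 13 after 30% attrition.

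**Step 1. Which number is net of attrition?** For unequal clusters, DE = 1 + ((CV² + 1)m − 1) x ICC, with CV² + 1 = 1.4225.
- m = 18 x 0.7 = 12.6: DE = 1.846 and 2.692, the stated 1.85 and 2.69.
- m = 13: DE = 1.875 and 2.749, close but not the stated values.

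So the stated design effect rests on the post-attrition cluster size. Sixty preschools then give 60 x 12.6 = 756 to 60 x 13 = 780 children, rounded in the article to about 800. The 800 is an analysed number.

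**Step 2. Reproduce the stated detectable effects.** Detectable d = (1.960 + 0.842) x √(2 x DE x f / n per arm). The article does not name its variance formula, so two were tried: f = 2(1 − r) for a change score and f = 1 − r² for baseline adjustment (ANCOVA). With 400 per arm:
- Change score, ICC 0.10: 0.252 (r 0.7) and 0.291 (r 0.6). This is the stated 0.25-0.30.
- ANCOVA, all four combinations: 0.192-0.260. This is not the stated range.

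The change score is therefore taken as the plan's formula. It also fits the time-by-group interaction test in the Primary aim section.

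**Step 3. Apply the plan's own attrition to 800 recruited.** 800 x 0.7 = 560 analysed, or 280 per arm; m = 560/60 = 9.33; DE = 1.61 and 2.23.

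| ICC | r | d, 400 per arm | d, 280 per arm | d, 280 per arm, ANCOVA |
|---|---|---|---|---|
| 0.05 | 0.6 | 0.241 | 0.269 | 0.241 |
| 0.05 | 0.7 | 0.209 | 0.233 | 0.215 |
| 0.10 | 0.6 | 0.291 | 0.316 | 0.283 |
| 0.10 | 0.7 | 0.252 | 0.274 | 0.252 |

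Power under the change score, 400 versus 280 per arm:
- ICC 0.10, r 0.6, d = 0.30: 82% versus 76%.
- ICC 0.10, r 0.7, d = 0.25: 79% versus 73%.
- ICC 0.05, r 0.6, d = 0.25: 83% versus 74%.

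The loss is modest because all 60 clusters remain and the design effect falls as clusters shrink. Holding DE at 1.85-2.69 with 280 per arm would overstate it, at 0.249-0.347.

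**Step 4. Seven months, change score.**
- All 1,200 analysed (600 per arm, m = 20, DE 2.37-3.74): d = 0.193-0.280. The lowest value is at ICC 0.05, r 0.7.
- 30% lost (1,200 x 0.7 = 840; 420 per arm, m = 14, DE 1.95-2.89): d = 0.209-0.294. ANCOVA gives 0.193-0.263.

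**Step 5. Recruitment that matches 800 analysed.** 60 x 18 = 1,080 by the plan's own cluster size, or 800/0.7 = 1,143. For 1,200 analysed, 1,200/0.7 = 1,714.

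These are normal approximations. Using t with 58 degrees of freedom adds about 0.003-0.006 to each d.

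**The case against.** The strongest reply is that 800 is a floor. The article invites all 3- to 5-year-olds in each participating preschool, and 60 preschools at the median of 18 hold about 1,080 children aged 3 to 4. The 18 counts children in a preschool, not children recruited, so the step from 18 to 13 might include families who decline. That would make 800 the enrolled number. This reading does not rescue the text: the article speaks of attrition and of children for analysis, and if the 30% covers non-consent, nothing is left for loss over 18 months.

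A reader might infer that the stated detectable effects are simply not delivered. The figures do not support that. With 560 analysed, three of the four change-score combinations stay within 0.30 and the fourth exceeds it by 0.016. With baseline adjustment all four stay at or below 0.283.

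A reader might also infer that the 7-month claim is false, because most combinations do not reach 0.20. The sentence is worded as a best case, and the best case holds with 1,200 analysed. After 30% loss it misses by 0.009 under the change score and still holds under ANCOVA. The article gives no separate attrition rate for 7 months; carrying over the 18-month rate is one reading of the reference to the assumptions above, and the pessimistic one.

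What stands is the recruited-versus-analysed inconsistency and a modest power cost. The reply is also right that the per-arm figure is already labelled as for analysis. What needs correcting is the recruitment wording beside 800 and, in the abstract, beside 1,200.

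**Conclusion.** The inconsistency is real: one figure does two jobs, and the section's own design effect shows that it is the post-attrition number. If recruitment stopped at 800 and 30% were lost, the detectable d at 18 months would be 0.23-0.32 instead of the stated 0.25-0.30. The plan's worst combination (ICC 0.10, r 0.6) would lose about 6 percentage points of power for d = 0.30. The 7-month 0.20 should be read as the most favourable case, within a range of 0.19-0.28 with no loss or 0.21-0.29 with 30% loss.

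This rests on the change-score variance, inferred because it reproduces the stated range; on 60 preschools being retained; and on 30% meaning loss of enrolled children. Design, randomisation, outcomes and analysis are unaffected. The severity is moderate or minor.

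**What to change.** Correct the text in the Participants section and the abstract, in one of two ways.

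- Label 800 and 1,200 as analysed numbers and state the matching recruitment numbers separately: about 1,080-1,143 aged 3 to 4 and about 1,700 in total. At the median of 18 per preschool, 60 preschools hold only 1,080 children aged 3 to 4, so these targets would need nearly full consent or larger or additional preschools.
- Keep 800 and 1,200 as recruited numbers and restate the detectable d as about 0.23-0.32 at 18 months and 0.21-0.29 at 7 months. Say that 0.20 is the most favourable case and which attrition rate applies at 7 months.

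Either way, name the variance formula and say whether the 30% covers non-consent, loss after enrolment, or both. The abstract's 0.20-0.30 should follow the chosen version. The cost is a few sentences and, under the second option, slightly less favourable figures. That option requires no extra enrolment; if the main model adjusts for baseline, 560 analysed gives about 0.22-0.28.
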